#### Weeks 1 and 2—Baseline

For the first 2 weeks participants will be instructed to wear the actigraphy monitor and complete the daily sleep diaries to obtain baseline data.

#### Weeks 3 and 4—Intervention 1

Participants will be instructed to use their designated MP3 player at bedtime. Once the play button is pressed, the audio file will automatically play a continuous loop throughout the duration of their sleep. Participants will continue to wear the actigraphy monitor and complete the sleep diaries as in Weeks 1 and 2. If participants find that the audio file prohibits them from sleeping, they are to discontinue its use and to contact the investigator within 24 h. The MP3 players will come with an accompanying USB cable to allow for the participants to charge the device if needed. The actigraphy monitors, which can hold a charge up to 30 days, will be charged by the investigator. In the unlikely event that the monitor fails, whatever data is collected will still be used. However, since it is unclear if there is a dose effect for BBF or music for that matter, participants will not be asked to recapture any missing data as it could impact the outcome measures. If a participant forgets to wear the monitor, they will still be required to complete the sleep diary questionnaire and note it in the questionnaire.

#### Appointment 2—Equipment exchange

At the conclusion of Week 4 participants will be scheduled for an appointment to exchange the sleep actigraphy monitor and MP3 player and complete the PSQI for Intervention 1. Before departing, participants will be given:

1) A newly charged sleep actigraphy monitor.2) One MP3 player pre-loaded with the designated audio file based on group assignment.

#### Week 5—Break

For the next week, participants will be instructed to abstain from using any audio stimulation at bedtime but to continue to wear the sleep actigraphy monitor and to complete the daily sleep diaries.

#### Weeks 6 and 7—Intervention 2

The investigator will contact the participant to instruct them to commence using their second intervention. Just as in Weeks 3 and 4, participants will use their respective audio intervention while wearing the actigraphy monitor and completing the sleep diaries. If the music or sound technology prohibits the participant from sleeping, the participant is to discontinue its use and contact the investigator within 24 h.

#### Final appointment

The participant will be scheduled to return all equipment. The investigator will check the online survey dashboard to ensure that all sleep diaries have been completed. Participants will then complete the PSQI for Intervention 2 and Post-Study Questionnaire (Table 2).

**Table 2 T2:** Data collection procedure.

**Action**	**Initial appointment**	**Weeks 1 and 2**	**Weeks 3 and 4**	**2nd appointment**	**1 week break**	**Weeks 6 and 7**	**Final appointment**
Screening, consent and randomization	X						
Participant demographic questionnaire	X						
National Sleep Foundation sleep diary		X	X		X	X	
Philips Actiwatch Spectrum Pro actigraphy monitor		X	X		X	X	
MP3 player with intervention 1			X				
MP3 player with intervention 2						X	
Pittsburgh Sleep Quality Index	X			X			X
Post-study questionnaires							X

### Outcomes measures

The primary aim of this study is to assess if an audio program that has theta and delta BBFs arranged in an order that mimics a healthy adult hypnogram will improve sleep quality. To subjectively measure improvement in sleep quality, the PSQI total scores from Interventions 1 and 2 will be compared to baseline to note any statistically significant differences. This score will also be correlated with the sleep efficiency percentage scores taken from the sleep actigraphy monitor as a secondary validation. To objectively measure improvement in sleep quality, sleep efficiency percentage calculated from the sleep actigraphy monitor will be used. Even though 80 to 85% is considered good sleep efficiency, improvement in sleep efficiency will be determined by identifying any statistically significant changes when compared to the participant's baseline where there was no intervention. Sub measures of sleep efficiency such as sleep latency, number of minutes awake after sleep onset, and number of times awaken throughout the night will be analyzed individually. Data collected from the National Sleep Foundation Sleep Diary will be assessed to see if there are any relationships between exercise, medication use, napping, sleepiness during the day, mood, alcohol, food and caffeine intake, timing of caffeine intake, and bedtime routine and the various sleep outcomes. The Post-Study Questionnaire will be used for informational purposes to assess the participants' experience, perception of the technology, and the feasibility of conducting Phases 3 and 4.

Based on the findings of the primary aim, the secondary aim of this study is to map out a plan for a series of feasibility studies to support the development of a customizable all-night audio track to induce sleep, sustain sleep and to provide a structure waking. First, if Phase 2 shows that the theta/delta combination with appropriate breaks for REM and timing did not sync appropriately due to each participants' unique sleep cycles, this step will be repeated using theta BBF only as theta will allow participants to fall back to sleep in the event they have a longer sleep latency or if awaken throughout the night. If Phase 2 shows efficacy with using the theta/delta combination, Phase 3 will next incorporate theta, alpha and beta BBFs, respectively, at the end of a 6-, 7-, or 8-h audio track to assess if it can trigger a structured waking process. For this phase the attention will be focus more on the ending of sleep such as awakening time and feeling upon awakening. In this case it may not be necessary to use BBFs for the entire night but to simply add a structured waking protocol near the end of an audio track. If Phase 3 proves successful, Phase 4 will combine lessons learned from Phases 1, 2, and 3 to create a customized all-night audio track starting with alpha and theta BBFs, that will transition to intermitted halting of theta and delta BBFs, and end with theta, alpha and beta BBFs. The ideal participant for this study would be persons with insomnia with the hope of using this technique later for persons with sleep phase disorder, non-24-h circadian rhythm disorder, irregular sleep wake disorder, shift work disorder, and/or jet lag disorder. Given that close assessment of sleep stages will be imperative to determine if the brainwaves are in fact being entrained, this study would be conducted within a sleep lab. According to Jirakittayakorn and Wongsawat (29), it may be possible to use electroencephalograms, electro-oculogram, and electromyograms without full polysomnography as they are sufficient for scoring sleep stages and offer better comfort for participants. Although this will be time consuming, equipment intensive, and would require much from the participant, a substantially smaller sample size may be adequate if data from the previous phases were found to be significant. If sleep actigraphy data from the previous phases proved to be consistent and reliable, Phase 4 could also include a hybrid approach of using actigraphy for 1 week and polysomnography later to truly assess if entrainment is taking place.

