#### Cohort 1 (n 106) unblinded

Group 1: Baseline → theta/delta BBF alone → 1 week break → music aloneGroup 2: Baseline → music alone → 1 week break → theta/delta BBF alone

Since the participants in Cohort 1 will know when they are receiving the intervention, it could be argued that their outcomes are due to a placebo effect, therefore a second cohort using a different group of participants will be used.

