#### Pittsburgh Sleep Quality Index questionnaire (PSQI)

Given that actigraphy distinguishes wakefulness from sleep based on movements and that there is a possibility that a person with poor sleep quality may stay awake while lying still, the Pittsburgh Sleep Quality Index questionnaire will be used. The PSQI is the most commonly used measure for subjective self-report sleep quality. In a study that examined test-retest reliability in a sample of 76 individuals with insomnia over a period of 2 days to several weeks, the PSQI showed a correlation of 0.87 for global score (34). This 24-item questionnaire captures “overall” subjective sleep quality and will be used before and after each intervention. This instrument gives an accumulative score based on seven subcomponents: subjective sleep quality, sleep latency, sleep duration, habitual sleep efficiency, sleep disturbances, use of sleeping medication, and daytime dysfunction (35). The total score ranges from 0 (good sleep quality) to 21 (poor sleep quality) with a 0–3 scoring range for each of the seven subcomponents (35). To assess significance, baseline scores will be compared to music alone, BBFs alone, and music with BBF.

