Actual values and change from baseline in the different Sleep Actigraphy report outcome variables will be summarized by time point and sequence group using descriptive statistics. Analysis will be conducted for the following variables: number of hours in bed, total number of hours asleep, number of minutes it took to fall asleep, percent efficiency of sleep, number of minutes awaken after sleep onset, and total number of times awaken after falling asleep. Sleep efficiency will be used as the main indicator for improvement of sleep quality and will be calculated by dividing the amount of time spent asleep (in minutes) by the total amount of time in bed (in minutes) and multiplying it by 100. Study parameters include sleep latency <30 min, wakefulness after sleep onset <30 min, decreased frequency in number of awakenings, total sleep time >6 h and sleep efficiency >80%.

Qualitative measures of sleep obtained from the PSQI will be analyzed using descriptive statistics. As for the National Sleep Foundation Sleep Diary entries, summary statistics will be provided at the different data collection time points. To further improve the precision of the estimates, items from the National Sleep Foundation Sleep Diary scores and light exposure (sleeping at night vs. sleeping during the day) may be entered into the model as additional covariates. To assess if the participants' personal characteristics' affect the outcome a two-step modeling approach will be followed. First, the effect of each demographic variable will be evaluated separately in a series of separate MMRM models that include each study outcome as the dependent variable and the demographic characteristic and time as predictors. All demographic factors will then subsequently be entered into a MMRM model that also incorporate intervention, period, sequence as fixed effects, and study participant as a random effect.

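### The PSQI analysis is described in three incompatible ways, and every stated PSQI test is against baseline only, so it cannot separate a BBF effect from music, time or expectation

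*Protocol article*

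**What the plan says.** The protocol article describes the PSQI analysis in three places.

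- **PSQI instrument section:** "To assess significance, baseline scores will be compared to music alone, BBFs alone, and music with BBF". The grouping is by audio type, and a significance test is intended.
- **Outcomes measures:** "the PSQI total scores from Interventions 1 and 2 will be compared to baseline", with statistical significance as the criterion. A test is again intended, but the grouping is by Intervention 1 and Intervention 2.
- **Power analysis and data analysis plan:** "Qualitative measures of sleep obtained from the PSQI will be analyzed using descriptive statistics". No test is named.

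In the study procedure, Intervention 1 and Intervention 2 are the headings for Weeks 3 and 4 and for Weeks 6 and 7. At the second appointment participants "complete the PSQI for Intervention 1"; at the last one, "Participants will then complete the PSQI for Intervention 2". What a participant hears in each period depends on the sequence. Group 2, for example, follows "Baseline → music alone → 1 week break → theta/delta BBF alone", and Group 1 takes the same two files in the opposite order.

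The data analysis plan also describes a crossover mixed model with fixed terms for intervention, period and sequence and a random term for participant. It does not name the PSQI as an outcome of that model. The Aims section states the primary aim as improvement relative to a control group and to no intervention.

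**The concern.** There are two problems.

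1. **Three descriptions that do not agree.** There are three audio conditions but only two numbered interventions, so the instrument section and the outcomes section do not define the same comparison as written. Testing in two places also conflicts with description only in the third. An analyst could follow any of them and claim to be on plan.
2. **The reference is always baseline.** Neither section that calls for a PSQI test states a comparison of BBF with music. A fall in PSQI from baseline can come from time in the study, from expectation or, for music with BBF, from the music itself. The article's own background makes this plausible. In Phase 1, 80% of participants felt that they fell asleep faster, whichever group they were in. In a cited sham-controlled trial, insomnia severity fell in both groups without a significant difference between them (p = 0.656).

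At stake is the subjective half of the primary aim: a significant PSQI change could be reported as an effect of BBF when the test performed cannot show that.

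**Working it through.** The plan gives no PSQI sample size, SD or power, so there is no stated figure to reproduce.

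**Step 1: what each period contains.** The sequences come from the Cohort 1 and Cohort 2 sections. The arms are equal: 106/2 = 53 and 62/2 = 31.

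| Group | n | Intervention 1 (Weeks 3–4) | Intervention 2 (Weeks 6–7) |
|---|---|---|---|
| 1 | 53 | BBF alone | music |
| 2 | 53 | music | BBF alone |
| 3 | 31 | music | music with BBF |
| 4 | 31 | music with BBF | music |

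The share on BBF-containing audio is 53/106 = 50% in each period of Cohort 1, 31/62 = 50% in each period of Cohort 2, and 84/168 = 50% in each period overall.

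**Step 2: what each comparison estimates.** Let b and m be the PSQI changes due to BBF-containing audio and to music alone, and p1 and p2 the period effects. Effects are taken as additive, without carryover.

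- By period, sequences pooled: Intervention 1 = (b + m)/2 + p1; Intervention 2 = (b + m)/2 + p2. Their difference is p1 − p2, which contains nothing about audio.
- By audio type: BBF = b + (p1 + p2)/2; music = m + (p1 + p2)/2. Their difference is b − m.

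With p1 = p2 = 0:

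| Truth | Pooled Intervention 1 | Pooled Intervention 2 | BBF by audio | Music by audio | BBF − music |
|---|---|---|---|---|---|
| m = −2, b = 0 | −1 | −1 | 0 | −2 | +2 |
| m = 0, b = −2 | −1 | −1 | −2 | 0 | −2 |

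The pooled period means are the same under opposite truths. Grouping by audio type separates them.

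**Step 3: why grouping by audio type is not enough.** Each by-audio change from baseline still carries (p1 + p2)/2. With m = 0, b = −2, p1 = −0.5 and p2 = −1, the BBF change is −2 − 0.75 = −2.75 and the music change is 0 − 0.75 = −0.75. The difference is still −2. In Cohort 2, if adding BBF to the music does nothing, then b = m, and testing music with BBF against baseline is simply a test of music.

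**Step 4: illustration of size.** The assumptions are two-sided 0.05, 84 participants (the number required for Cohort 1 before attrition; 42 per sequence), SD of change 3 and within-person correlation 0.5. The article gives neither the SD nor the correlation. Proportion of 5,000 simulated trials with a significant result:

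| Truth | Pooled period vs baseline | BBF vs baseline | BBF vs music, within participant |
|---|---|---|---|
| m = −2, b = 0 | about 84% | 5% | over 99% (music better) |
| m = 0, b = −2 | about 82% | 100% | 100% |
| m = b = −1 | about 85% | about 85% | 5% |

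The third row is the case of a common change from any cause. The baseline test for BBF is usually significant, while the contrast with music keeps its 5% level.

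The 85% depends on the SD. With power ≈ Φ(1/(SD/√84) − 1.96):

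- SD 2: Φ(4.58 − 1.96) = above 0.99
- SD 3: Φ(3.06 − 1.96) = 0.86
- SD 4: Φ(2.29 − 1.96) = 0.63

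**The case against.** A reader might infer that the plan commits itself to a pooled-by-period PSQI analysis, and so cannot show a BBF effect at all. The document does not support that.

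- The outcomes section never mentions pooling sequence groups. It may simply name which two post-intervention scores are set against baseline, leaving the grouping to the instrument section.
- Each PSQI total follows one known audio file. Only a pooled period mean would be mixed, and the scores collected fully support a comparison by audio type.
- The rest of the article thinks in audio conditions: the design section lists four, and the mixed model separates intervention from period and sequence. One modelling step refers to every study outcome, which could be taken to include the PSQI.
- Sleep efficiency is the main indicator, so wording on the PSQI does not decide the primary conclusion.

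All of this stands, and it makes the pooling problem conditional. It does not reconcile testing in two sections with description only in the third, and it does not supply a PSQI comparison of BBF with music. Nor can the inconsistency be left to an unseen analysis plan, since the article itself states the conflicting versions.

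**Conclusion.** The point holds as an inconsistency together with a weak criterion; the article does not establish a planned invalid analysis. Three sections disagree on how the PSQI is grouped and on whether it is tested. If periods were pooled over sequences, the mix would be exactly 50/50 at planned enrolment, and a change could not be credited to BBF; unequal dropout between sequences would shift that share. Under any reading, the stated tests against baseline do not meet the Aims section's requirement of comparison with a control.

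The formulas assume additive effects and no carryover. The percentages are illustrative: they rest on an assumed SD, correlation and effect size, and the pooled column also on pooling that the article does not state. They show the direction of the problem and do not forecast this trial's error rate. This should be corrected, but it does not threaten the analysis of sleep efficiency.

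**What to change.** Use one description in the PSQI instrument section, the data analysis plan and Outcomes measures:

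- Analyse PSQI by audio condition within each cohort, using the crossover mixed model already planned (intervention, period and sequence fixed, participant random).
- Base any claim of a BBF effect on PSQI on the within-participant contrast with music alone: BBF alone against music in Cohort 1, and music with BBF against music in Cohort 2.
- Keep the contrasts with baseline as supportive.
- Keep Intervention 1 and Intervention 2 as period labels only.

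The cost is a few sentences, a little extra analysis and a stricter criterion for PSQI improvement. No new data or visits are needed, and sleep efficiency stays the main indicator. One limit remains: Cohort 1 is unblinded, so its contrast with music removes only the expectation common to both audio files. The blinded contrast in Cohort 2 is the cleaner of the two, and the report should say so.

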## Aims

The primary aim of this study is to assess if an audio program that has theta and delta BBFs arranged in an order that mimics a healthy adult hypnogram will improve sleep quality as evidence by an increase in sleep efficiency score when compared to a control group and no intervention. The author hypothesizes that when similar participants are matched and compared, those using BBF will have similar outcomes.

Based on the findings of the primary aim, the secondary aim of this study is to map out a plan for a series of future feasibility studies to support the development of a customizable all-night audio program to induce sleep, sustain sleep and provide a structure waking for persons with poor sleep quality (Figure 3).

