#### Cohort 2 (n 62) blinded

Group 3: Baseline → music alone → 1 week break → music embedded with theta/delta BBFGroup 4: Baseline → Music embedded with theta/delta BBF → 1 week break → music alone

Upon completion of both cohorts, a matched group analysis will be conducted to assess the differences between no intervention vs. music alone vs. theta/delta BBF alone vs. music embedded with theta/delta BBF.

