### Power analysis and data analysis plan

For Cohort 1, since the study is comparing three measures, a 2 × 3 mixed ANOVA (between and within subject factor) will be used. The parameters for this analysis were as follows: (1) power of 1—β = 0.85, (2) level of significance of α = 0.05, (3) an autocorrelation parameter (i.e., average correlation) ranging from 0.3 to 0.7 (in increments of 0.2), and (4) a standardized effect size (F) ranging from small (0.1) to medium (0.25) in 0.05 increments. Using GPower software, the sample size estimates range from *n* = 52 (when the correlation of the repeated measures = 0.7 and the standardized effect size is *F* = 0.25) to *n* = 116 (when the correlation of the repeated measures = 0.3 and the standardized effect size is *F* = 0.1). For this study a sample of 106 will be sufficient (84 required, plus 25% for attrition bringing the total to 105 and the addition of 1 to make both arms equal in number).

For Cohort 2, assuming there is no difference in mean sleep efficiency score (i.e., mean difference = 0) between the interventions (BBF only, music with BBF) a sample size of 61 participants (plus 1 to make group equal in number *n* = 62) would be needed to declare with at least 80% power that the intervention effect in BBF only is the same as in music with BBF. Given that Cohort 1 is *n* = 106 and that propensity score matching with replacement will be implemented to make the groups comparable, the final test for intervention effect will be carried out with a power in excess of 80%.

For this two-period 2-arm cross-over design where each subject gets both treatments and repeated outcome measurements over time, a linear mixed model with repeated measures (MMRM) approach will be used. Unless otherwise stated, all statistical tests will be 2-sided with the probability of a Type I error not to exceed 0.05. Descriptive statistics will be used for all quantitative and qualitative variables at all data collection points. Continuous variables will be tabulated using N, mean, standard deviation or standard error (as appropriate), median, minimum, and maximum values. For categorical variables, frequency counts and percentages will be presented.

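### Improvement in the main endpoint is judged against a baseline that always comes first and is never randomised, and the randomised BBF–music contrast is not named as the criterion

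*Protocol article*

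**What the plan says.** The Power analysis and data analysis plan section names the endpoint: "Sleep efficiency will be used as the main indicator for improvement of sleep quality". Outcomes measures then defines success on it: "improvement in sleep efficiency will be determined by identifying any statistically significant changes when compared to the participant's baseline where there was no intervention". The subjective measure is handled in the same way: "the PSQI total scores from Interventions 1 and 2 will be compared to baseline to note any statistically significant differences".

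The Aims set a wider test, an "increase in sleep efficiency score when compared to a control group and no intervention".

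Every group starts with the no-intervention period. Group 2 in Cohort 1, for example, follows "Baseline → music alone → 1 week break → theta/delta BBF alone", and Group 4 in Cohort 2 follows "Baseline → Music embedded with theta/delta BBF → 1 week break → music alone". Groups 1 and 3 differ from these only in the order of the two audio files.

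For the analysis, the protocol describes a two-period, two-arm crossover fitted by a mixed model, with a final step that will "incorporate intervention, period, sequence as fixed effects, and study participant as a random effect". The Cohort 1 sample size rests on something else: "since the study is comparing three measures, a 2 × 3 mixed ANOVA (between and within subject factor) will be used".

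**The concern.** The aim has two comparators, a control and no intervention. The stated criterion uses only the second, and that one is not protected by randomisation. Anything that changes between the baseline weeks and the later weeks counts as an audio effect: the passage of time, getting used to the watch, or expecting to sleep better. Participants enter on an ISI score of at least 13, so some regression to the mean may add to this. Blinding in Cohort 2 does not help a comparison with baseline, because baseline has no audio at all.

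The protocol's own account of Phase 1 shows why this matters: 80% of participants felt that they fell asleep faster, whichever group they were in. Under the rule as written, music alone could be declared to improve sleep on the same evidence as BBF. The decision has consequences, because the four-phase plan makes Phase 3 depend on Phase 2 showing efficacy.

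**Working it through.** **Inputs.** From the power section: two-sided α = 0.05; Cohort 1 power 0.85; correlation ρ of 0.3, 0.5 or 0.7; F from 0.10 to 0.25; 84 required; Cohort 2 n = 62. Assumed, because the protocol gives neither an SD nor an expected drift: a common shift d after baseline of 0 to 0.3 SD, unrelated to the audio content.

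**1. Reproduce the 84.** For a within-participant test with m = 3 levels and 2 groups, λ = F²·N·m/(1−ρ), with df = 2 and 2(N−2).
- With F = 0.15, ρ = 0.5 and N = 84: λ = 0.0225 × 84 × 3 / 0.5 = 11.34, power 0.857. N = 82 gives 0.848, so 84 is the smallest even number that reaches 0.85.
- The protocol does not say which F and ρ lie behind the 84. F = 0.15 and ρ = 0.5 are inferred because they reproduce it.
- Three levels means that baseline is one of them.

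**2. Chance of a false improvement with inert audio.** For a paired t-test of intervention minus baseline, the noncentrality is δ = d√n / √(2(1−ρ)). With n = 84 and ρ = 0.5 the denominator is 1, and the critical value is 1.989 (df 83). Improvement is one tail of a two-sided test, so the reference rate is 2.5%.

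| Shift d (SD) | δ at ρ = 0.5 | ρ = 0.3 | ρ = 0.5 | ρ = 0.7 |
|---|---|---|---|---|
| 0 | 0 | 2.5% | 2.5% | 2.5% |
| 0.1 | 0.917 | 12% | 15% | 22% |
| 0.2 | 1.833 | 33% | 44% | 65% |
| 0.3 | 2.750 | 63% | 78% | 94% |

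A simulation of 10,000 trials per setting agrees. At d = 0.3, ρ = 0.5 and n = 84, BBF and music are both declared to improve in 65% of trials. In the same trials the period-adjusted BBF–music test rejects at its nominal level: 4.7% to 5.5% over n = 62, 84 and 106, all three ρ and shifts of 0 to 0.3 SD.

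**3. Can the planned model give the controlled contrast?** For two periods, the columns are intercept, BBF versus music, period and sequence: 4 columns, rank 4. Nothing is aliased.

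**4. What 84 completers give for BBF versus music.** The detectable difference at 85% power is (1.960 + 1.036)/√84 = 2.996/9.165 = 0.327, so about 0.33 SD of the within-person difference. At ρ = 0.5 that SD equals the SD of a single measurement.

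At the same F = 0.15 and ρ = 0.5, the power of this contrast depends on how the three means (none, music, BBF) are spread:
- Music gives half of BBF's gain, means (0, d/2, d): SD of means = d/√6, so d = 0.15 × √6 = 0.367. BBF–music = 0.184, δ = 0.184 × 9.165 = 1.68, power about 38%.
- Music inert, means (0, 0, d): SD of means = d√2/3, so d = 0.318. BBF–music = 0.318, δ = 2.92, power about 82%.
- Music equal to BBF, means (0, d, d): BBF–music = 0, yet the three-level omnibus test keeps its planned power of 0.857.

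**The case against.** The sentence under Outcomes measures can be read more mildly. It follows a remark about the usual 80 to 85% standard and may only be choosing relative change over an absolute cut-off. Controlled comparisons are planned elsewhere: the Abstract names Cohort 1 music as the control, the Study design section compares all four conditions, and the power section commits to a crossover mixed model. This stands. A reader might infer that the trial has no controlled analysis, and the protocol does not support that. The defect is that the controlled analysis is never made the criterion.

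A reader might also infer that the mixed model is aliased. That is true only if baseline is entered as a third period alongside a no-intervention level. The protocol describes two periods and two treatments, and that model is of full rank.

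Regression to the mean should not be pressed as sufficient by itself. Selection is on ISI, whereas actigraphic sleep efficiency is first recorded after enrolment. The effect reaches the endpoint only as far as the two share temporary variation. Drift, habituation and expectation need no such link.

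Finally, this is a feasibility study, which lowers the stakes. But its result is meant to decide whether Phase 3 goes ahead.

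**Conclusion.** The concern holds in this form: the written criterion for improvement rests on an uncontrolled before–after comparison and omits the control that the Aims require, while a sound randomised contrast is already available. The inflation depends on a shift that the protocol does not quantify. At ρ = 0.5 with 84 completers it runs from none (2.5%) at zero shift, through 15% at 0.1 SD, to 78% at 0.3 SD.

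The sample size does not settle the matter. The 84 was obtained from an omnibus test that includes baseline and can succeed when BBF and music are identical. It would go too far to say that the controlled contrast is necessarily underpowered: 38% and 82% are both consistent with F = 0.15 and ρ = 0.5, depending on what music does.

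**What to change.** - Reword Outcomes measures so that a claim that BBF improves sleep efficiency requires a significant within-participant BBF minus music difference, adjusted for period and sequence, in each cohort: BBF versus music in Cohort 1, and music with BBF versus music in Cohort 2.
- Test both cohorts whatever the other shows. Unblinded Cohort 1 should not be the gatekeeper, because the protocol added blinded Cohort 2 to answer the placebo argument against Cohort 1.
- Keep change from baseline, for sleep efficiency and PSQI, as a supporting comparison labelled as uncontrolled for time.
- State that the 84 comes from a three-level omnibus test that includes baseline. For BBF versus music, give the sensitivity as about 0.33 SD of the within-person difference at 85% power with 84 completers, with power of about 38% to 82% over the two patterns above.
- Give the matching figure for Cohort 2, whose 62 was sized for a different question. The same formula gives 2.996/√62 = 0.38 SD if all 62 complete.

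The cost is wording and restated sensitivity; the planned schedule already collects the data. The claim against no intervention becomes supportive only, and the stated sensitivity for the controlled contrast is less favourable than the present text suggests. Requiring significance in both cohorts also makes the overall claim harder to reach than either test alone.
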